#### Stabilization surgery

Participants allocated to the *stabilization surgery group* will undergo capsular plication and labrum repair surgery as appropriate. Capsular plication surgery will involve the placement of suture anchors into the bony glenoid with sutures passed through the shoulder joint capsule to secure the redundant capsule to the glenoid fossa, effectively ‘tightening’ the joint. Labrum repair will be performed using standard suture anchors incorporating the plication where appropriate. All participants will receive the same post-operative clinical care from the surgical team to monitor progress and deal with any complications that may arise. Standard care includes review at 1, 3 and 6 months post surgical examination/intervention.

#### Physiotherapy

All participants will receive the same post-operative physiotherapy protocol aimed at improving shoulder muscle function based on a pre-prepared treatment algorithm. All participants will be immobilized in a sling for four weeks following the surgical procedure but will be allowed to perform controlled scapular and glenohumeral joint movements within ranges which would not compromise a capsulolabral repair. Thus restrictions on post-operative treatment to protect the surgical procedure will apply to all participants. Thereafter, the aim of physiotherapy treatment will be to improve the function of the rotator cuff muscles by an active home-based exercise program. The treatment algorithm allows the physiotherapist to choose specific exercises directed to the rotator cuff or to improve their function by incorporating exercises which involve the entire kinetic chain. To ensure accurate exercise performance multimodal feedback (visual, biofeedback, taping) can be utilized. The type, load and frequency of exercises will be individually tailored to the needs of each participant by the physiotherapist who will monitor and upgrade the exercises as rotator cuff muscle function improves. A maximum of 12 treatment sessions with the physiotherapist over a maximum period of six months after surgery will be conducted.

### Outcome measures

#### Primary outcome measure

Pain and functional impairment, measured using the Western Ontario Shoulder Instability Index (WOSI), will be the primary outcome. The WOSI is a disease specific, self-administered questionnaire consisting of 21 items assessing the physical symptoms associated with shoulder instability (10 items) as well as the impact of shoulder instability on sport/recreation/work (4 items), lifestyle (4 items) and emotional state (3 items). It was rigorously developed using patient input, demonstrates good construct validity and excellent reliability and is responsive to change [3].

#### Secondary outcome measures

Data on four secondary outcomes will be collected:global perceived effect assessing participant-reported improvement measured on an 11 point scale from −5 (“vastly worse”) to +5 (“completely recovered”) [23].active external and internal shoulder rotation range of motion measured using digital photography [24–26] This method was chosen over goniometry as it is less likely to exacerbate shoulder symptoms due to the shorter time required to complete measurements.isometric external and internal shoulder rotation strength measured using a hand-held dynamometer which has been shown to exhibit acceptable reliability when tested on patients with strength deficits [27]number of episodes of post-operative shoulder dislocation. An episode of shoulder dislocation will be defined as separation of the articular surfaces of the shoulder joint which require assistance to be relocated.

All outcome measurements will be re-assessed 6 months after randomization by a research assistant who will be blind to treatment group allocation. At 12 and 24 months after randomization pain and functional impairment, participant-reported improvement and number of shoulder dislocations sustained will again be re-assessed by a blinded assessor.

### Sample size

The sample size was calculated assuming a 10.4% change on the WOSI given a standard deviation of 18% change, a significance level of 5% and assuming a 10% (worst-case) loss to follow-up. A 10.4% change in total WOSI score represents the minimally important change required to represent a clinically significant improvement [28]. This is a conservative sample size estimate as it ignores the additional power conferred by the longitudinal analysis that is to be used in this study.

### Sequence generation

An allocation assignment schedule will be prepared prior to commencement of the clinical trial using random numbers generated with the ralloc command in the Stata statistical package [29]. The random allocation schedule will be prepared by a member of the research team not associated with identification of potential participants or any aspects of recruitment, treatment or assessment of participants, and will remain concealed until the analysis is complete. Allocation will be in randomly permuted blocks.

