## Methods/Design

### Design

A two-arm, double-blind randomized controlled clinical trial will be conducted. 140 patients will be recruited in two study centres and will undergo a clinical assessment to assess potential eligibility for the study. Potentially eligible patients who consent to participate will undergo arthroscopy and those with arthroscopic evidence of capsulolabral damage will be randomly allocated during the procedure into one of two groups: a *stabilization surgery* group and a *control* group. The primary outcome (pain and functional impairment) and secondary outcomes (participant-reported improvement and number of shoulder dislocations sustained) will be evaluated at baseline and 6, 12 and 24 months after randomization. Additional secondary outcomes of shoulder rotation range of motion and strength will be evaluated at 6 months after randomization. Ethics approval to conduct this study has been granted by the NRES Committee London-Stanmore and NRES Committee Wrightington, Wigan and Leigh.

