### Interventions

140 participants will be recruited and randomly allocated to either a:stabilization surgery group (70 participants). Participants in this group will receive an arthroscopic investigation of the shoulder joint followed by arthroscopic stabilization surgery and postoperative physiotherapy rehabilitation.control group (70 participants). Participants in this group will receive an arthroscopic investigation of the shoulder joint followed by postoperative physiotherapy rehabilitation.

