#### Primary analyses

The primary analyses will be conducted on an intention-to-treat basis. The focus will be on estimation of the effect [31] at 2 years, but hypothesis tests will also be conducted. Between-group comparisons will be conducted using a linear model in which the outcome is a linear function of a dummy-coded variable representing group membership (stabilization surgery or control group) and baseline score [32]. For the outcomes of pain and functional impairment, participant-reported improvement and incidence of shoulder dislocations, all of which are measured at baseline and 6, 12 and 24 months, mixed models will be used. The mixed models will incorporate a random intercept for subject. A negative binomial model will be used to analyze data on the incidence of dislocations. A sensitivity analysis will be conducted in which multiple imputation is used to account for missing data [33, 34].

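### The two-centre trial's stated primary model omits centre, and the article does not report whether allocation is stratified by centre; adding centre is a cheap, small gain in precision

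*Protocol article*

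**What the plan says.** The Design section states that "140 patients will be recruited in two study centres". The Interventions section allots 70 participants to each arm.

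The Sequence generation section describes a schedule prepared in advance with the Stata ralloc command and adds "Allocation will be in randomly permuted blocks". It neither states nor rules out strata. The Arthroscopic examination section has theatre staff open a sealed envelope once eligibility is confirmed, without saying whether there is one set of envelopes or one per hospital.

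The Primary analyses section specifies a model in which "the outcome is a linear function of a dummy-coded variable representing group membership (stabilization surgery or control group) and baseline score". For outcomes measured repeatedly it moves to mixed models with a random intercept for subject. No fixed or random term for centre appears.

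**The concern.** The article goes beyond naming a class of model. It lists the covariates and the random effect, and the one structural feature of the design that is known for every participant, the hospital, is not among them.

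There is reason to expect some centre effect on the WOSI. The operation is chosen to suit what the surgeon finds, and the exercises are tailored by the treating physiotherapist, so delivery depends on local staff even under common protocols.

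What follows depends on how the schedule was built:

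- **Not stratified by centre.** Permuted blocks balance the arms overall but not within each hospital. A centre difference then sits in the residual, and part of it passes into the treatment estimate through chance imbalance.
- **Stratified by centre.** The arms are nearly balanced within each hospital, so the true sampling variance excludes the centre component. A model without centre still counts that component as residual, and its standard error is slightly too large.

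Precision is what is at stake. Neither case threatens validity.

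**Working it through.** **1. Reproduce the sample size.** Inputs from the Sample size section: a difference of 10.4 ("assuming a 10.4% change on the WOSI"), an SD of 18 ("given a standard deviation of 18% change"), a 5% significance level and 10% loss. Power and sidedness are not stated.

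n per arm = 2 × (1.960 + 1.282)² × 18² / 10.4² = 62.95, so 63. Allowing for loss, 63 / 0.90 = 70 per arm, or 140 in total.

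Two-sided 5% with 90% power therefore gives the stated 140. Two-sided 80% gives 108, two-sided 85% gives 120 and one-sided 90% gives 116. I take 90% as the implied power.

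The standard error with 63 analysed per arm is 18 × √(2/63) = 3.21, and the power is 90.0%.

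**2. Assumptions.** The documents give neither the share p of patients from one centre nor the WOSI difference D between centres. I take p = 0.5 as the main case and D = 3, 5 and 10 percentage points, the scale on which the target is 10.4. The SD of 18 is treated as the overall SD, so it already contains any variation between centres.

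**3. Gain from putting centre in the model.** The share of variance due to centre is R² = p(1 − p)D² / 18². The standard error is multiplied by √(1 − R²). For D = 10, R² = 0.25 × 100 / 324 = 0.077, and 3.21 × √0.923 = 3.08.

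| D (points) | R² | Reduction in standard error | Power with centre (90.0% without) |
|---|---|---|---|
| 3 | 0.7% | 0.35% | 90.2% |
| 5 | 1.9% | 1.0% | 90.6% |
| 10 | 7.7% | 3.9% | 92.2% |

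For a 70:30 split the powers are 90.2%, 90.5% and 91.8%. For 80:20 they are about 90.2%, 90.4% and 91.4%.

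**4. Chance imbalance if one unstratified list serves both centres.** With 70 patients per centre, the number from one centre allocated to surgery has a hypergeometric SD of √(70 × 0.25 × 70/139) = 2.97, and a 95% range of 29 to 41. The between-arm difference in centre share has SD 2 × 2.97 / 70 = 0.085. A simulation of one blocked list, with assumed block sizes of 2 to 8, also gave 0.085.

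Multiplying by D gives a shift in the unadjusted estimate with SD 0.25, 0.42 or 0.85 points. The 95% limits are about ±0.5, ±0.8 and ±1.7, against the target of 10.4.

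**5. The shift is part of the standard error.** With all 70 per arm the standard error is 18 × √(2/70) = 3.04. For D = 10, 0.85² / 3.04² is about 0.078, which matches the R² of 7.7% in step 3 up to rounding. Steps 3 and 4 describe the same loss and must not be added together.

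**6. If the list is stratified.** The standard error from the model without centre is too large by the factor 1/√(1 − R²), which is about 0.35%, 1% or 4% for D = 3, 5 or 10.

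**The case against.** The strongest reply is that this is a condensed article. A reader might infer from its silence that randomisation is unstratified. The text does not support that: a single ralloc schedule can hold strata, and the full protocol may specify them. Block sizes are likewise a detail that an article commonly leaves out. This part of the reply stands, so the point rests on the model, whose terms the article does list.

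A reader might also call centre a strong prognostic factor, or suppose that the two hospitals differ in case mix. The documents say neither. They set common eligibility rules and one physiotherapy protocol, and baseline WOSI, already in the model, would absorb some of any case-mix difference. That stands too. D is an assumption, and its upper value of 10 is almost as large as the target effect, so it should be read as an extreme.

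Finally, the article says that the sample size takes no credit for the longitudinal analysis, so the trial is not short of power for want of a centre term. That is correct. None of this is a reason to leave centre out: the adjustment costs almost nothing and is suitable under either form of allocation.

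**Conclusion.** The point holds as a modest improvement to a stated model. In a two-centre trial the primary model lists group, baseline score and a subject intercept, and omits centre. With an equal split and centre differences of 3 to 10 points, including centre raises power by about 0.2 to 2 percentage points from an implied 90.0%, and reduces the standard error by about 0.35% to 4%. Unequal splits give slightly less. These figures rest on assumed values of p and D and on an SD of 18 that includes variation between centres. D should be read as the difference left after baseline adjustment.

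A reader might infer that omitting centre biases the treatment effect or inflates the type I error. It does neither. With an unstratified list the comparison remains valid and is only less precise; with a stratified list the test is slightly conservative. It would also be wrong to read the 0.85-point shift as error on top of the standard error, since it is a component of it. The sample size of 140 needs no change.

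**What to change.** Add centre (two levels) as a fixed effect to the primary WOSI model, and to the other linear and mixed models, and record this before unblinding. State whether the allocation schedule and the envelopes are stratified by centre.

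The cost is one degree of freedom: with 126 analysed and three terms (intercept, group, baseline), the residual degrees of freedom in the single-time-point model go from 123 to 122. The covariate can be added even if recruitment has begun, because each participant's hospital is known. The calculation above does not cover the negative binomial model for dislocations, so whether to include centre there is left to the trial team.

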### Adverse events

Participants in this clinical trial will be subjected to the risks associated with orthopaedic surgery under general anaesthesia. However, participation in this clinical trial will not entail additional risks beyond those associated with standard care options for atraumatic shoulder instability at the clinical sites involved in the study. Information regarding adverse events will be monitored throughout this clinical trial and reported on a regular basis to the Trial Management Group and Steering Committee associated with the Stanmore Clinical Research Centre. Both closed and open questioning will be utilized to seek information from participants and physiotherapy staff involved in post-operative treatment, all of whom will be unaware of whether stabilization surgery was performed.

### Statistical analyses

#### Interim analysis

One interim analysis of efficacy will be conducted when 50% of the estimated sample has completed one year follow-up assessment. The decision to continue the trial or stop the trial early will be made by the Trial Management Group and Steering Group, informed by an analysis of the Haybittle-Peto boundary [30]. The p-value threshold for this interim analysis will be set at 0.001. The final analysis will be evaluated at the significance level specified in the sample size calculation i.e. p < 0.05.

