**Methods/Design:**

140 participants will be recruited. Patients with feelings of insecurity (apprehension) at their shoulder joint, which is not the result of a collision injury, with physical signs of shoulder joint instability will be invited to participate. Consenting participants will undergo arthroscopic investigation of the shoulder joint. Patients with capsulolabral damage will be randomly allocated using a concealed allocation procedure to either stabilization surgery immediately following the arthroscopic examination or no additional surgical procedure. All participants will then receive the same postoperative physiotherapy protocol for up to 6 months. Outcomes (pain, functional impairment and number of shoulder dislocations sustained) will be evaluated prior to surgery and, together with participant-reported improvement, again at 6, 12 and 24 months after randomization. The primary endpoint will be pain and functional impairment at 2 years. Participants, clinical staff (but not surgeons) and assessors will be blind to whether stabilization surgery was performed. Data analysis will be conducted on an intention-to-treat basis with the focus on estimation of the effect.

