On the other hand, some studies indicate that surgery is not successful for the treatment of atraumatic shoulder instability and can result in longer term detrimental effects. A small prospective observational study did not find significant functional improvement in young athletes with multidirectional instability following surgery [17] and failure rates of up to 60% have been reported following thermal capsulorraphy surgery [18]. In addition, there is some evidence that patients who have undergone unsuccessful surgery for atraumatic instability and subsequently proceed with conservative rehabilitation have worse outcomes than those who are initially treated conservatively [6]. It has also been suggested that in younger patients whose atraumatic instability is primarily due to abnormal, unbalanced muscles forces on the shoulder joint surgical intervention may contribute to early degenerative changes. [19, 20].

In summary, the limited evidence available suggests that, in patients with traumatic shoulder instability, surgical intervention followed by physiotherapy rehabilitation is the most effective management strategy but in patients with atraumatic instability without structural damage to shoulder capsule or ligaments, surgery is not helpful or detrimental. The role of surgical intervention in patients with atraumatic shoulder instability associated with capsulolabral damage is still unclear. A robust clinical trial is required to determine if surgical intervention is necessary to provide optimal short, medium and longer term outcomes for these patients.

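### The efficacy look is timed on one-year follow-up while the primary endpoint is at 2 years, and the plan does not secure the 24-month comparison if the boundary is crossed

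*Protocol article*

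**What the plan says.** The Abstract (Methods/Design) fixes the time point: "The primary endpoint will be pain and functional impairment at 2 years". The Primary analyses section agrees: "The focus will be on estimation of the effect [31] at 2 years, but hypothesis tests will also be conducted". WOSI is scheduled at baseline and at 6, 12 and 24 months.

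The Interim analysis section sets the look by a different clock: "One interim analysis of efficacy will be conducted when 50% of the estimated sample has completed one year follow-up assessment". It then gives the consequence, "The decision to continue the trial or stop the trial early will be made by the Trial Management Group and Steering Group", and adds that a Haybittle-Peto boundary informs that decision. The thresholds are explicit: "The p-value threshold for this interim analysis will be set at 0.001", and "The final analysis will be evaluated at the significance level specified in the sample size calculation i.e. p < 0.05".

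That section does not name the outcome or time point to be tested at the look. Nor does it say whether a stop would end recruitment only or follow-up as well.

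**The concern.** The rule that may end the trial is tied to one-year follow-up, and the question the trial was set up to answer is at 2 years. A Haybittle-Peto boundary limits false positives for the hypothesis tested at the look. If that hypothesis concerns mainly 6- and 12-month WOSI, the boundary says nothing about a benefit that is present at one year and gone by two.

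The meaning of an early stop is also left open. If it includes ending follow-up, the 24-month comparison is lost or truncated, and this cannot be repaired afterwards. Durability matters to this trial: the Discussion says it is unknown whether adding surgery gives better long-term outcomes, and the Study objectives hypothesise both short- and long-term improvement.

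**Working it through.** **Inputs.** Sample size section: difference 10.4 points on the WOSI percentage scale, SD 18, significance level 5%, loss to follow-up 10%. Interventions section: 140 participants, 70 per arm. Interim analysis section: trigger at 50%, so 70 participants (35 per arm); threshold 0.001, taken as two-sided.

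**1. The plan's own figure.** Power is not stated. With 90% power and two-sided 5%:

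n per arm = 2 × (1.960 + 1.282)² × 18² / 10.4² ≈ 63; 63 / 0.90 = 70; total 140.

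This matches exactly. Two-sided 80%, 85% and 95% power give 108, 120 and 174, so 90% is the inferred value.

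**2. Difference needed to cross at the look.** Assumptions: the SD of 18 also holds at 12 months, and the comparison is unadjusted.

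SE = 18 × √(2/35) = 4.30; boundary = 3.29 × 4.30 ≈ 14.2 points.

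With 10% loss (31.5 per arm) the boundary is 14.9 points. The design difference is 10.4.

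**3. Chance of crossing**, 1 − Φ(3.29 − δ/4.30), for a true 12-month difference δ with 35 per arm:

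| δ (points) | Chance of crossing |
|---|---|
| 10.4 | 19% (16% with 10% loss) |
| 13 | 39% |
| 15.6 | 63% |
| 18 | 81% |

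These figures depend only on the 12-month effect. They are the same whether the 24-month effect is equal, smaller or zero.

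**4. How much 24-month data exists at the look.** The accrual period is not given. Assume uniform accrual of 140 over T months. Half have one-year data at month T/2 + 12, and the number with 24-month data is then 140 × (T/2 − 12)/T, or 0 if that is negative.

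| T (months) | Randomised at the look | With 24-month data |
|---|---|---|
| 24 or less | 140 | 0 |
| 30 | 126 | 14 |
| 36 | 117 | 23 |
| 48 | 105 | 35 |
| 60 | 98 | 42 |

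The 24-month count is always below the 70 who trigger the look. When T is 24 months or less, everyone has already been randomised, so stopping the trial could only mean shortening follow-up.

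**5. Type I error.** If both looks tested one hypothesis, the overall level of 0.001 followed by 0.05, from the bivariate normal, is 0.0500 to 0.0510 across correlations from 0 to 0.9. Alpha inflation is negligible and is not the problem.

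**The case against.** The strongest reply is that this is a condensed article. The interim endpoint and the handling of participants after a stop are commonly left to the full protocol, the analysis plan or a monitoring charter, none of which is shown. The article does schedule blinded assessment at 24 months, and it keeps the allocation schedule concealed until the analysis is complete. The threshold is strict, the decision is discretionary, and a one-year benefit is part of the stated hypothesis.

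Much of this stands. The use of 12-month data is inferred from the trigger, not stated. But the article does fix the trigger, the boundary, the threshold and the consequence, and it keys them to a time point other than the primary one. Neither the assessment schedule nor the concealment sentence says what happens after an interim stop.

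Four stronger readings are tempting, and the documents do not support them:

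- **That 19% is the chance of stopping.** It is the chance of crossing. The boundary only informs the committees, so the chance of a stop cannot be derived.
- **That there is a 31% chance of a false success.** A true 12-month difference of 12 points gives a 31% chance of crossing, but pairing it with no effect at 24 months is an assumption without support in the documents.
- **That the Background predicts late harm in these patients.** It does say "surgery is not successful for the treatment of atraumatic shoulder instability and can result in longer term detrimental effects", but attributes this to some studies. Its summary ties unhelpful or detrimental surgery to patients without structural damage and calls the role of surgery in capsulolabral damage unclear.
- **That inflation of the estimate is specific to the one-year look.** The mean estimate given crossing is 16.5 when the truth is 10.4, but a 0.001 boundary on 24-month WOSI with the same 70 participants would inflate it about as much.

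**Conclusion.** The concern holds in a limited form and should be fixed. The efficacy look is timed on one-year follow-up, the primary endpoint is at 2 years, and nothing in the text secures the 24-month comparison once the boundary is crossed. The rule makes crossing a minority outcome at the design effect, about one in five, but likely if the one-year effect is large.

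The mismatch of time points rests on the text alone. The crossing figures rest on 35 per arm, SD 18 at 12 months, a two-sided threshold and no adjustment; the planned baseline adjustment and mixed models would change them. The scarcity of 24-month data rests on uniform accrual. A reader might infer that the trial is bound to end without answering its question. The documents support only that it could, because the committees keep discretion and may continue follow-up.

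**What to change.** Add to the Interim analysis section:

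1. The outcome and time point tested at the look.
2. That the efficacy conclusion rests on the 24-month WOSI contrast.
3. That crossing the boundary at the one-year look can at most close any remaining recruitment, with all randomised participants kept blinded, followed to 24 months and included in the primary analysis.

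Alternatively, apply the 0.001 boundary to the 24-month WOSI contrast.

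The cost is one paragraph; 140 participants and the final 0.05 level stay as they are. The first option makes the early look less decisive, and under uniform accrual of 24 months or less it has no practical effect, because recruitment is already complete. The second brings the look later: half the sample reaches 24 months at T/2 + 24, which is after the end of accrual unless T exceeds 48 months. If accrual is expected to be that fast, the sponsor should consider whether an efficacy look is worth keeping.
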